# Data management, self-assessment

# Creation of Case Report Form (CRF)

Co-investigators etc. will complete a CRF. Creation of CRF will be performed immediately after each examination. If there will be any mistake in a CRF, an investigator must report it to the study office.

# Self-assessment of CRF

1. Co-investigators etc. must validate details of each category in a CRF.
2. If there is any contradiction in a CRF, a document which explains the reason of contradiction must be created.
3. A principal investigator and co-investigators etc. must sign after validation and confirmation of a completed CRF.

# Trasfar and storage of CRF

A principal investigator must transfar the completed CRF to the study office following a fixed procedure, and store a copy of the completed CRF.

# Procedure of CRF correction

If a CRF needs to be corrected, a principal investigator must submit a document of any change or correction in a CRF to the study office, and store a copy of the document.

# Competing interests of fundings

This study is a joint research with Ohki Pharmaceutical Company and Tohoku University Knowledgecast※, and funding is provided by Ohki Parmaceutical company. GBE/MST supplement, GBE supplement, and placebo will also be provided by this pharmaceutical company.

COI of this study must be described in the informed consent form, following the Declaration of Helsinki (World Medical Association) and the Ethical Guidelines for Medical and Biological Research Involving Human Subjects (Ministry of Health, Labour and Welfare, Japan). COI management will follow the guideline in each institution. COI of researchers in Tohoku University will be controlled by COI management committee, Tohoku University.

The funders have no role in the study design, data collection and analysis, decision to publish, or preparation of the manuscript.

※ This is an affiliated company of Tohoku University. Description of this company is to promote social utilization of research outcomes, consultation, and human resources development.

# Description of contract company

Product management and distribution is performed by Ohki Pharmaceutical Company.

# Management of personal information

# Application purpose of personal information

For obtaining appropriate results, the personal information will be stored both during study period and follow up period.

# Utilization method （Anonymization methods）

**（１）Criteria of personal information**

| subject | | definition | example | existence |
| --- | --- | --- | --- | --- |
| Personal information | | 1. Objects which can identify a specific individual by itself | Name, Picture of face, etc. | ■yes  □no |
|  |  | 1. Objects which can identify a specific individual by matching with other information | Data using a correspondence table |  |
|  |  | 1. Those containing a personal identification code | Genom data, etc. | □yes  （specify：　　　）  ■no |
|  | Special care-required personal information | Those containing a race, creed, social status, medical history, criminal record, fact of having suffered damage by a crime, or other descriptions prescribed by cabinet order as those of which the handling requires special care so as not to cause unfair discrimination, prejudice or other disadvantages to the person. | Medical record, Medical receipt, Medical examination data, Partial genom data* | ■yes  （specify：laboratory data）  □no |

* Genom data with medical information, such as single nucleotide polymorphism, monogenic disease, and sensitivity of medication, may be applicable in personal information with consideration.

**（２）Anonymization**

■yes（to（3））

□no（reason：　　　　　　　）

□other（specify：　example：non-identifiable processed information prescribed in the Act on the Protection of Personal Information Held by Incorporated Administrative Agencies）

**（３）Type and method of anlnymization**

■1）Anonymized（with the correspondence table for identifiable of a certain person stored in Tohoku University）

Method：The correspondence table in which personal information such as name and identification number will be deleted and alternative code or number will be addressed is produced in an institution of Tohoku University. A personal information manager appropriately stores it so as not to leak to the outside.

□2）Anonymized（those of deidentified, and the correspondence table is stored in another facility）

　Method：The correspondence table in which personal information such as name and identification number will be deleted and alternative code or number will be addressed is not stored in an institution of Tohoku University (The correspondence table is stored in another facility and is not stored in Tohoku University). If the correspondence table is stored in another institution of Tohoku University, this case is not applicable.

□3）Anonymized（those of deidentified and without the correspondence table）

Method：The correspondence table in which personal information such as name and identification number will be deleted and alternative code or number will be addressed is not produced.（The codrrespondence table is not produced in any facilities in this study）

□4）Other　（specify：　　　　）

# The safety management responsibility system （Security control action）

Personal information manager in Tohoku University

　・Name：[name]

　・Affiliation：Department of Aging Research & Geriatric Medicine, Smart Aging Research Center

　・Qualification：Medical doctor

Security method：Storage with paper or electronic medium. Anonymized correspondence table and raw data are separately and appropriately stored.

Including 4 issues described below:

　・Physical safety control (A data management PC is securely stored in a rocked area of a laboratory in the department. Prohibit transfering strage medium. Act prevention of robbery and leakage.）

　・Technical safety control (Restriction of the access to a data management PC. Software security against injustice access from outside of the facility）

　・Organization safety control (Restrict the access of personal information and the authority to the principal investigator and co-investigators）

　・Human safety control (Periodic education)

# Procedure of informed consent

# Informed consent to participants

Investigators must present and explain the informed consent document which was apploved by the institutional organization.

**（Matters to be included）**

① Name of the study, and description about approvement of the study by the institute director

② Name of the institutional organization and principal investigator

③ Explanation of the purpose and significance of the study

④ Procedures and expected duration of the study

⑤ Explanation of selected reason as a study participant

⑥ Description of any burdens, foreseeable risks, and benefits for a study participant

⑦ Disclosure of the right to withdraw the agreement with participation to the study

⑧ Statement that participation is voluntary, refusal to participate will involve no penalty or loss of benefits, and a participant can discontinue participation at any time without penalty or loss of benefits

⑨ Procedures of the disclosure of study information

⑩ Explanation of obtaining and viewing study information those will not affect the personal information of other participants and the study originality

⑪ Procedures of handling personal informations（including the method when anonymizing）

⑫ Methods of storing and discarding study samples and information

⑬ Conflict of interest situation (source of funding, foreseeing conflicts of interest, and association with relevant organizations such as researchers）

⑭ Explanation of responding to consultations etc. from study participants and relatives etc.

⑮ Contents when there is any economic burden or reward for the study participants etc.

⑯ Explanation of handling any personal results (including incidental findings) in which this study may potentially obtain critical knowledge, such as personal health status and heritable genetic features

⑰ Explamation of any supports and contents, if applicable, against health problems caused by the study, in case of the study contains any invasive procedures

⑱ Explanation of any possibilities in those the samples and information obtained from study participants may be used in an unspecified future study or may be provided to other research institutes

# Agreement

Reserchers must explain the research, give them time to think carefully, confirm that the study participants have a good understanding of the content of the reserach, and then ask them to participate in the study. If the study participant agrees to participate in the examination, the consent form will be signed by oneself.

The original documents are stored by the study director of the research institute and a copy is passed to the study participant.

# Procedures for receiving informed consent from a substitute, etc.

A substitute is not allowed. The informed consent must be obtained from the principal.

# Procedures for obtaining an informed ascent

　N/A

# Procedures of disclosure

N/A

# Preparation and storage of records related to the transfer of samples and information

N/A

# Burdens, foreseeable risks (including possible adverse events) and benefits, comprehensive assessments of these subjects, and counterplan of minimizing burdens and risks

1. **Predicted benefits**

Study participants may get a partial health information, as the MRI findings will be checked by radiology specialists and the results will be provided.

1. **Foreseeable risks**

There are foreseeable risks and disadvantage regarding performed examinations, a temporal restriction of participating in the examinations, and an expected economical burden by using public transportation.

Risks and adverse events regarding blood sampling

Procedure of blood sampling will be the same as that performed in a health chek-up. Foreseeable events will be described below:

1. Bleeding from the site of puncture will be seen, and blueing may be expected. Counterplan is to perform complete astriction for 5min.

2. Tape eruption of skin may be occured because of a patch used on the site of puncture. Counterplan is to be asked if a participant had a risk of tape eruption. In that case, vinil tape will be used, instead of normal tape.

3. There is a possibility of allergic response by using alcohol rubbing cotton. Counterplan is to be asked about the existence of alcohol allergy. In that case, chlorhexidine swab will be used instead of alcohol swab.

4. There is a possibility of vasovagal reflex by pain or stress causing bad feeling and consciousness loss. Counterplan is to be asked as if a participant had a risk of vasovagal reflex before blood sampling. A participant may have a rest after blood sampling.

5. There is a possibility of the nerve injury along with blood sampling. The symptom of nerve injury is finger numbness and pain caused by injured peripheral nerves by needle puncture. The frequency is reported about 1/6000. Because it is anatomically difficult to completely prevent it, the blood sampling will be performed at an outpatient site following a recommended procedure as the ideal prevention. In case of the incident, a participant may consult a clinic using own medical insurance.

Risks and adverse events regarding MRI

1. The MRI apparatus may cause injury by iron materials existing in or on the body. Counterplans are described below:

・Ask several times about operation history, internal metals, and cardiac pacemaker, by means of document and interview.

・Confirm no metals on the body befor the examination.

・Inform that the examination can stop anytime during the procedure if a participant will feel any abnormalities.

2. Since the MRI apparatus has strong magnetic field, metallic materials can be pulled and may physically injure a participant. Counterplans are described below:

・Metallic material without anchoring must not be stored in the MRI room.

・The exclusinve stuffs of MRI must control the procedures in the MRI room which has protective methods against expecting risks.

3. There is a possibility of finding any critical diseases, such as brain tumore, brain absess, brain hemorrhage, brain infarction, brain artery aneurysm, arteriovenous malformation, etc., by analysis of MRI. If any of such abnormality will be found, an investigator will inform the participant about to ask a doctor.

4. During MRI procedures, undesired noise, magnetic field, change of body temperature, and unconfortable position in narrow space may cause discomfort. As counterplan of discomfort, a participant can use a buzzer for alart any bad feeling. If a buzzer sounds, an operator must stop the procedure, and a doctor must check a participant’s condition. In case of difficultiness, the MRI procedure can be cancelled.

Risks and adverse events regarding GBE and GBE/MST

　GBE, sesame extract, and turmeric oil have been used as suppliments, and their safety has been established. No critical adverse event was reported. Digestive symptoms and thirsty have been reported as side effects. These symptoms will diminish after 3-4 days of cessation. If such side effects are strong, participation of this study can immediately be stopped.

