# Rationale

The primary endpoint of this study is to determine the impact of GBE/MST on cognitive function in healthy adults, which will be assessed by the Wechsler Memory Scale-Revised (WMS-R) after 24 weeks of GBE/MST administration. The WMS-R is designed to indicate a standard deviation of 15 if its normal average score is 100. In the present study, when the estimated alteration rate of the standard deviation was 1%, the difference in the average score was 6. Cohen’s calculation formula with an effect size of 0.4 at a significance level (α) of 0.05 and a detection power (1-β) of 80% yielded a sample size of 44 participants. Considering a dropout rate of 20%, 159 participants will be required (53 participants in each group).

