# Statistical analysis

# Statistical methods

(1) Analysis of cognitive function

The average of total WMS-R score at the endpoint will be compared among the GBE/MST, GBE, and placebo groups using one-way analysis of variance (ANOVA) and Tukey's test. The difference between the total score at baseline and at the endpoint will be compared among the three groups using multivariate ANOVA (MANOVA).

(2) Analysis of brain morphology

Total cerebral cortical volume will be calculated from the T1-weighted structural images using the SPM12 software. The average alteration in total volume from baseline to the endpoint will be compared among the three groups. Using the CONN toolbox (https://web.conn-toolbox.org/) implemented in MATLAB, functional connectivity (FC) between two regions of interest (ROIs) within the DMN will be analyzed by means of ROI-to-ROI analysis.

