# Methods

1. Intervention

〇Active

・GBE/MST capsule (commercially known as “Brain assist ®︎”)

Ginkgo biloba extract, sesame oil, Piper longum extract, reduced sugar syrup, refined fish oil containing docosahexaenoic acid with gelatin, spice extract, glycerin, glycerin fatty acid ester, beeswax, caramel color, vegetable lecithin from soybean

4 kcal, proteins: 0.2g, lipids: 0.3g, carbohydrates: 0.2g, salt: 0.0008g

・GBE capsule (commercially known as “Icho-ba Ekisu”)

Ginkgo biloba extract, reduced sugar syrup, gelatin, glycerin fatty acid ester, caramel color, tocotrienol lecithin from soybean

5 kcal, proteins: 0.2g, lipids: 0.4g, carbohydrates: 0.2g, salt: 0.0009g

Both have a dosage of two capsules per day. Both the products will be provided by Ohki Pharmaceutical Company and will have similar shapes, colors, and tastes. The package containing the products will not have any information to avoid participant bias.

〇Placebo

Placebo will be made in matched for size, color and taste to the GBE/MST capsule and GBE capsule.

Reduced sugar syrup, refined fish oil containing docosahexaenoic acid with gelatin, spice extract, glycerin, glycerin fatty acid ester, beeswax, caramel color, vegetable lecithin from soybean

5 kcal, proteins: 0.2g, lipids: 0.5g, carbohydrates: 0.1g, salt: 0.0009g

1. **Dosage and administration**

Participants in the GBE/MST group will consume two capsules of the GBE/MST supplement. Participants in the GBE group will consume two capsules of GBE supplement. Participants in the placebo group will consume two capsules of placebo.

1. **Adverse effects and cessation criteria**

The adverse effects will be screened throughout the study period. Headache, dizziness, tinnitus, diarrhea, nausea, gastrointestinal symptoms, high blood pressure, excessive thirst, dyspnea, chest pain, bradycardia, and upper respiratory infection have been reported as adverse effects of GBE [5]. Interestingly, participants consuming GBE showed a lower incidence of adverse events when compared with those consuming a placebo [10]. The study will be terminated if any grade 3 adverse event is reported. If a participant shows any adverse events and requests a refusal, the study will be terminated.

1. **Schedule**

At registration, written informed consent will be obtained from the participants. Subsequently, cognitive function will be evaluated using the MoCA-J. Participants with a score of ≧26 will be eligible for inclusion.

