Standard blood and urine tests will be performed to check for health status. Body measurements, grasping power of both the hands, two-step test, and functional reach test will be performed at baseline and at the endpoint (24 weeks).

Cognitive tests will be completed by the participants at baseline and at the endpoint. The WMS-R and its lower domains will be used to measure total memory function and assess individual function (digit span indicates verbal memory and the tapping span indicates visual memory). Stroop Color and Word Test and Trail Making Test will be employed to assess executive functions such as restraint-related functions and sustained attention, respectively.

Magnetic resonance imaging (MRI: Achieva Intera 3T, Philips Healthcare, Quasar Dual, The Netherlands) will be performed at baseline and at the endpoint. T1 weighted magnetization-prepared rapid acquisition gradient echo (MPRAGE) structural images (matrix: 240 × 240, repetition time: 8.70 ms, echo time: 3.1 ms, flip angle: 8°, field of view: 256 × 256 × 180 mm, 162 slices, voxel size: 0.7 × 0.7 × 0.7 mm, and scan duration: 5 min 15 s) will be acquired to collect 3D structural datasets. Resting state functional MRI (rs-fMRI: T2*-weighted gradient-echo planar imaging, matrix: 64× 64, repetition time: 3000 ms, echo time: 30 ms, flip angle: 90°, field of view: 220 × 220 ×218 mm, 34 slices, voxel size: 3.44 × 3.44 × 3.40 mm and 197 volumes with 5 min superimposition) with closed eyes will be performed to analyze the DMN.

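### The adverse-event wording does not separate stopping the capsules from leaving the study, so participants who stop may have no 24-week WMS-R score and the comparison may rest on completers

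*Protocol*

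**What the plan says.** Three sentences in the Protocol govern what follows an adverse event.

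- In the section on burdens and foreseeable risks, under the risks of GBE and GBE/MST: "If such side effects are strong, participation of this study can immediately be stopped". The sentence before it describes the expected course: "These symptoms will diminish after 3-4 days of cessation".
- In Methods, under adverse effects and cessation criteria: "If a participant shows any adverse events and requests a refusal, the study will be terminated".
- In the same place: "The study will be terminated if any grade 3 adverse event is reported".

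On measurement, the schedule in Methods says "Cognitive tests will be completed by the participants at baseline and at the endpoint", with the endpoint at 24 weeks. There is no cognitive visit in between. Statistical methods compares mean total WMS-R at the endpoint across the three groups by one-way ANOVA and Tukey's test. The sample-size rationale allows for loss: "Considering a dropout rate of 20%, 159 participants will be required".

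After an adverse event, the section on responding to it continues observation of symptoms and laboratory abnormalities. It does not mention cognitive testing.

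**The concern.** The three sentences refer variously to participation and to the study. None refers to the capsules alone, and nothing elsewhere says that a person who stops the capsules is still asked to attend at 24 weeks. A site that follows the text could reasonably treat stopping as the end of all assessments.

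That matters here because the outcome has a single post-baseline measurement. Without it a participant has nothing to enter into the endpoint comparison, and any imputation could draw only on baseline data. An analysis plan can say how missing scores are handled, but it cannot recover scores that were never collected. If those who leave differ from those who stay, and do so unequally across arms, the groups compared at 24 weeks are no longer the groups that were randomised.

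**Working it through.** **The plan's own dropout figures.** 44 × 1.2 = 52.8, rounded up to 53 per group, and 3 × 53 = 159. A 20% loss from 53 leaves 53 × 0.8 = 42.4 per group. (Dividing instead, 44 / 0.8 = 55. The derivation of the 44 is a separate matter, and nothing below depends on it.)

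**Precision.** The standard error of a between-arm difference with SD 15 (sample-size rationale) is 15 × √(2/n):

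| n per group | Meaning | Standard error (points) |
|---|---|---|
| 53 | no dropout | 15 × √(2/53) = 2.91 |
| 44 | number the design aims to analyse | 15 × √(2/44) = 3.20 |
| 42.4 | 53 less 20% | 15 × √(2/42.4) = 3.26 |

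Against no dropout the increase is 3.26 / 2.91 = 1.12, or 12%. Against the planned 44 it is 3.26 / 3.20 = 1.02, or 2%.

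**Bias of a completers' comparison.** Let d be the proportion lost in an arm and D the amount by which stayers outscore leavers. The full-arm mean is the stayers' mean minus d × D, so the completers' mean is too high by d × D. The contrast between arms A and B is then off by d_A × D_A − d_B × D_B. The Protocol gives neither arm-specific losses nor leavers' scores, so both are assumptions:

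| Loss, arm A v arm B | Assumed gap D (points) | Shift (points) | Share of the 6-point difference |
|---|---|---|---|
| 20% v 20% | any, the same in both arms | 0 | 0% |
| 20% v 10% | 3.75 to 12, the same in both arms | 0.10 × 3.75 = 0.375 to 0.10 × 12 = 1.2 | 6% to 20% |
| 30% v 10% | 3.75 to 12, the same in both arms | 0.20 × 3.75 = 0.75 to 0.20 × 12 = 2.4 | 12.5% to 40% |
| 20% v 20% | 7.5 in one arm, 0 in the other | 0.20 × 7.5 = 1.5 | 25% |

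The last row shows that equal losses alone do not guarantee an unbiased contrast. The gap must also be similar across arms.

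**Feasibility of the remedy.** The Protocol expects the named side effects, digestive symptoms and thirst, to diminish within days of stopping. Many who stop could therefore still take a memory test at 24 weeks. The visit is already scheduled, and the section on rewards ties the full payment to completing the examinations at registration and 24 weeks.

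**The case against.** The strongest case against the point is that the Protocol states no rule removing people with side effects. The risk section says that participation can be stopped, and only if effects are strong, which reads as a safeguard for the participant. The sentence in Methods depends on the participant's own request, which is most naturally withdrawal. No text bars someone who stopped capsules from the 24-week test, and the payment rule encourages attendance. All of this stands. A reader might infer that everyone with a side effect must leave, but the documents do not say so. What remains is that the wording never separates product from participation, and nothing invites those who stop back for testing.

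A reader might also infer that losses will depend on the product. The Protocol's own evidence does not support that: Scientific rationale reports no difference between GBE and placebo in dropout due to adverse effects, and Methods cites fewer adverse events on GBE than on placebo. That evidence concerns GBE, and the meta-analysis described under Scientific rationale was in patients with Alzheimer's disease. GBE/MST is a different mixture, whose effects the Backgrounds section describes as not yet validated. Differential loss is therefore possible, but not shown.

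Finally, the 12% rise in standard error might be read as the gain from the fix. It is not. It compares planned loss with none, the 20% covers all causes and is already budgeted, and only those who agree to return would be recovered.

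Analysis sets and missing-data rules commonly belong to the SAP. Whether the 24-week score is collected after stopping belongs to the protocol.

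**Conclusion.** The point holds as one of unclear wording with a real consequence for data collection. As written, a participant who stops because of an adverse event may have no 24-week WMS-R, and the primary comparison may then rest on completers. The Protocol does not call its analysis completers-only; this follows from the single post-baseline measurement and the endpoint comparison.

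Under the assumed 20% v 10% losses and a common gap of 3.75 to 12 points, the contrast shifts by about 0.4 to 1.2 of the 6 points. With equal losses and a common gap the shift is zero. The other cases worked through are illustrations on the same footing. The direction is unknown, since the document does not show which arm would lose more or how leavers would score. No gain in precision can be quantified, because the share who would return is unknown. The change is worth making because it costs little and the lost scores cannot be recovered later.

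**What to change.** Reconcile the adverse-effects text in Methods with the GBE and GBE/MST risk text, so that each sentence says whether it ends the product, the individual's participation or the whole study. This includes the grade 3 sentence, which does not say whether it means the participant or the trial. The conditions under which capsules are stopped are not for this point to change.

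Then state that participants who stop the capsules are invited to the already planned 24-week WMS-R unless they withdraw consent, and that they are analysed in the group to which they were randomised. The right to withdraw is unaffected.

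The cost is wording in the protocol and consent form; no new visit is needed. There is one small downside: including people who stopped early can dilute the estimated effect relative to continued use.
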